### Study setting and sample selection

Participants will be recruited from acute and community settings across LHD 1 and LHD 2, NSW, Australia. Research sites are listed below in Table 2.

**Table 2 Tab2:** Research sites

	Acute		Community	
	Intervention	Control	Intervention	Control
LHD 1	Geriatric Rehab Unit (LHD1**HIS**1)	Geriatric Rehab Unit (LHD1**HCS**3)	Public Community Health Centre (LHD1**CIS**5)	Public Community Health Centre (LHD1**CCS**7)
	Medical ward at Hospital (LHD1**HIS**2)	Medical ward at Hospital (LHD1**HCS**4)	Non-public Home and Community Care (LHD1**CIS**6)	Non-public Home and Community Care (LHD1**CCS**8)
LHD 2	Medical ward at Hospital (LHD2**HIS**9)	Medical ward at Hospital (LHD2**HCS**11)	Public Community Health Centre (LHD2**CIS**13)	Public Community Health Centre (LHD2**CCS**15)
	Medical ward at Hospital (LHD2**HIS**10)	Medical ward at Hospital (LHD2**HCS**12)	Non-public Home and Community Care Service (LHD2**CIS**14)	Non-public Home and Community Care Service (LHD2**CCS**16)

Note: Hospital Intervention Site (*HIS*), Hospital Control Site (*HCS*), Community Intervention Site (*CIS*), Community Control Site (*CCS*). One full-time RN for 2 wards in one hospital and one full-time RN for 2 community service providers at one setting are allocated in each LHD

The 16 research sites were pair-matched (eight intervention, eight control) and selection was based on admission rates, patient profile, number of deaths per month/year, average length of stay and number of referrals from/to hospital and community. To minimise potential contamination of intervention the sites chosen are geographically separated. Both public funded and non-public sites are involved in this research, to maximise the generalisability.

All newly admitted patients to a site listed as an ‘intervention site’ will be offered facilitated ACP conversations, and all other sites will continue to deliver usual care (control sites).

Once potential participants are identified by inclusion and exclusion criteria (Table 3), a robust screening process will be applied which includes; patients with mental capacity and the ability to give valid informed consent as established by admitting medical officer or admitting RN by using Montreal Cognitive Assessment (MOCA) and Mini-Mental State Examination (MMSE). MOCA (26/30) and MMSE are done as part of new admission process (if a contemporaneous assessment has not already been completed by another unit/ward/department i.e. ED). Those who have a score of 10 or above will be nominated to participate. Those who have score of 10–24 (MOCA) and whose capacity is in question will be formally assessed by RN ACP Facilitators using NSW Capacity Tool Kit [22]. A conservative approach to recruitment will be applied. If capacity to consent is unclear for any potential participants these individuals will not be approached. Screening for potential participants will occur before consent has been obtained. This will prevent patients that are not defined as relevant to the aims of this research through the inclusion/exclusion criteria from being informed of a service they will not receive and/or overburdening people.

**Table 3 Tab3:** Inclusion and exclusion criteria for participants in this study

Group	Inclusion criteria	Exclusion criteria
Group 1: People with Chronic Diseases	▪ Patients aged ≥18 years old ▪ Admitted to the wards/community centres in participating hospitals and community settings, ▪ Identified in Medical Records as having a chronic health condition(s) (defined within this research project as; Diabetes, Congestive Heart Failure, Coronary Artery Disease, Chronic Obstructive Pulmonary Disease, Hypertension, Chronic Kidney Disease, Cancer, Frailty and Dementia. ▪ Patients who do not currently have an Advance Care Directive	▪ Women who are pregnant and the human foetus. ▪ Children and/or young people (< 18 years old). ▪ People highly dependent on medical care. ▪ People who are experiencing acute severe physical illness and/or an acute episode of mental illness (a diagnosis of anxiety alone may not exclude participation)
Group 2: Substitute Decision Makers (SDMs)	• ≥18 years old • Nominated as an SDM by people with chronic diseases at intervention site • The ability to give valid informed consent	▪ Children and/or young people (< 18 years old). ▪ People who are experiencing acute severe physical illness and/or an acute episode of mental illness (a diagnosis of anxiety alone may not exclude participation)
Group 3: Admitting Healthcare Professionals (MOs, RNs, &/or SW) at intervention sites (normalisation agents level one, or NA1)	▪ ≥18 years old ▪ The ability to give valid informed consent ▪ Working in a professional capacity admitting patients to one of the research units listed, or ▪ Employed and trained as a NA2 for this research study.	▪ Not working in one of the research units listed
Group 4: RNs delivering the intervention (referred to as ‘RN ACP Facilitators’) at intervention sites (normalisation agents level two, or NA2).	▪ ≥18 years old ▪ The ability to give valid informed consent ▪ Employed and trained as a NA2 for this research study.	▪ Not employed and trained as a NA2 for this research study

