### Design

The project is a quasi-experimental design with two groups: 1) intervention groups with RN ACP facilitators, and 2) control groups without RN ACP facilitators. See Fig. 1. Research Flow Chart below.

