#### Conversation 2 and more

All people with chronic diseases and their nominated SDMs who meet the inclusion criteria will be assessed by RN ACP facilitators for English Proficiency, cognitive impairment and acute episode of mental illness by asking the following questions as recommended by NSW Planning Ahead Tools [5].Do you remember and/or understand the ACP brochure given by MO or RN or SW?,Who should your doctor talk to about your medical treatment?You have a choice to have or not to have a conversation(s) with me. Do you want to have a conversation(s) with me?

RN ACP facilitators will begin with open ended questions exploring the person’s knowledge, attitude and desire to participate in ACP. RN ACP facilitators will also clarify the person’s goals and values; identification of whom should be involved in these conversations; and the person’s understanding of diagnosis, prognosis and preferences for treatment options and place of care.

According to responses, RN ACP facilitator will initiate and facilitate a series of conversations between person, the nominated SDM, treating medical team, and/or a Health Care Interpreter or appropriate Cultural Support Person if required. The components of ACP include personal details, Person Responsible, personal values about dying, directions about medical care, specific requests for organ and tissue donation, and authorisation with signatures in Section 1 to 5 in NSW Ministry of Health ‘Making an ACD’ [5]. A summary of outcomes of these conversations will be entered: 1) in the person’s medical record; 2) A Conversation Log; and 3) A ‘Conversation card’ which is a size of business card when folded and which will be carried in participating patient’s wallet/purse.

Ongoing commitment from participants is not required. The series of conversations are optional and consent to proceed will be checked repeatedly through the course of discussion. The post-evaluative surveys and interviews are also voluntary and are ‘one-off’ so do not involve ongoing follow up or appointment. All potential participants will have as much time as they require to consider participation, but at least 24 h between provision of information (written information statement and verbal explanation) and gaining written informed consent for participation is recommended in line with the National Statement on Ethical Conduct in Human Research [23] and Good Clinical Practice guidelines [24].

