#### Quantitative data analysis

Participant demographics and characteristics will be collected at each site and will be tabulated to show the distribution of participant characteristics between control and intervention sites (i.e. age, sex, primary reason for admission &/or chronic health condition). Continuous variables will be described by mean (standard deviation) if normally distributed and by median (interquartile range) otherwise. Categorical variables will be described by count (percentage). Group comparisons for continuous outcomes will be undertaken by either the Student t-test or Mann-Whitney U test. The Fisher’s Exact test will be used for categorical outcomes.

Baseline characteristics of study groups will be compared to assess similarity at study entry, thereby allowing for the identification of significant imbalances requiring adjustment during analysis. To account this and for clustering at the site level, multi-level regression models with mixed effects will be built to estimate interventional effect. For each model building process, variables found to be significantly associated with respective outcome measures in the univariable analysis at the 10% level will be retained in the final modelling.

As the primary predictor of interest, intervention effect will be forced into the multivariable modelling. Continuous outcome measures will be analysed using linear regression models. For binary outcome measures, analysis will be by binary logistic regression, while multinominal logistic regression will be used to analyse non-binary categorical measures. Model diagnostics will be conducted on all models.

All tests of significance will be set at 5%. Statistical analysis will be performed using Stata version 15.0 (StataCorp, College Station, TX, USA).

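### Formal capacity assessment is assigned to staff who work only at intervention sites, and the baseline list omits the admission cognitive score that would show a resulting imbalance

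*Protocol article*

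**What the plan says.** Study setting and sample selection describes screening in two steps. Admitting medical or nursing staff first establish capacity with MOCA and MMSE; this step is not limited to one arm. The scores are routine: "MOCA (26/30) and MMSE are done as part of new admission process", unless another unit has already done a current assessment. Patients scoring 10 or more are nominated.

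The second step is for doubtful cases: "Those who have score of 10–24 (MOCA) and whose capacity is in question will be formally assessed by RN ACP Facilitators", using the state capacity tool kit. If doubt remains, "If capacity to consent is unclear for any potential participants these individuals will not be approached".

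The Design section defines the comparison arm as "control groups without RN ACP facilitators". Table 3, Group 4, describes the facilitators as "RNs delivering the intervention (referred to as ‘RN ACP Facilitators’) at intervention sites". The same staff then deliver the service: "RN ACP facilitator will initiate and facilitate a series of conversations".

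Quantitative data analysis tabulates participant characteristics by arm, with the list given as "i.e. age, sex, primary reason for admission &/or chronic health condition". Baseline characteristics are then compared, "thereby allowing for the identification of significant imbalances requiring adjustment during analysis". Neither MOCA nor MMSE is named.

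**The concern.** A patient in the 10–24 band whose capacity is in doubt meets an extra decision at an intervention site. The facilitator may clear that patient for recruitment or may rule the patient out. No assessor is named who could take that decision at a control site. The recruited groups can therefore differ in borderline cognition because of how they were selected, separately from any difference between the sites' patients.

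Cognition plausibly affects whether someone completes a directive and how care is experienced. In a non-randomised study, protection against such a difference comes from the variables measured and adjusted for. Here the variable on which selection acts is already collected at admission, yet it is missing from the stated list. At stake are outcomes in recruited participants that can be linked to records: directive completion among the planned 144 + 144, and concordance of care with wishes where it is linked.

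**Working it through.** The plan gives no figure on this point, so there is none to reproduce. The check sets the sections side by side and then illustrates a possible size.

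**1. Is the step specific to one arm?** The sample selection section names one formal assessor, the facilitator. Design and Table 3 place facilitators at intervention sites only. As written, the step has no control counterpart. The article does not say in terms that control sites go without formal assessment; that follows from no other assessor being named.

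**2. Which way would it act?** This is not determined. If doubtful patients at control sites are simply not approached, facilitator clearance adds borderline patients to the intervention arm. But everyone scoring 10 or above is first nominated, so the facilitator's check can also remove patients. Control patients are invited to the survey or interview by post through an administrative officer, with no capacity step described there. If those invitations are ungated, the control arm could hold more borderline patients.

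**3. Would the listed characteristics show it?** Only in part. Dementia is one of the study's chronic conditions, so a large difference in recorded dementia would appear. A difference within the 10–24 band among patients without that diagnosis would not.

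**4. Which outcomes pass through the gate?**
- Audit of ACP related practice: records of everyone admitted to the 16 sites. It does not pass through the gate.
- Recruited participants: they pass through it. The sample size section sizes the directive outcome on 144 per arm, a 25% non-response rate and a 10-point change from 5%.
- Surveys: kept anonymous under Data management, so scores cannot be linked.

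**5. Illustrative size.** Let s be the borderline share in the intervention arm minus that in the control arm. Let p_b and p_o be directive completion in borderline and other participants. Then

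shift in arm difference = s × (p_b − p_o).

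All values of s, p_b and p_o below are assumptions, although 5% and 15% echo the planned baseline and follow-up rates.

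| s (points) | 2% vs 5% | 5% vs 15% | 0% vs 15% |
|---|---|---|---|
| 5 | −0.15 | −0.5 | −0.75 |
| 10 | −0.3 | −1.0 | −1.5 |
| 20 | −0.6 | −2.0 | −3.0 |

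Example: 0.20 × (0 − 15) = −3.0 points. If s is negative, every sign reverses. As a head count, 144 × 0.75 = 108 responders per arm, so 5% to 20% is 108 × 0.05 = 5.4 to 108 × 0.20 = 21.6 people.

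**The case against.** The strongest reply has four parts.

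First, directive prevalence is described as coming from an audit of all admitted patients, which has no capacity gate. This stands. A reader might infer that the audit result is biased by the facilitators' assessments; the documents do not support that. What remains open is the population: the sample size section sizes the directive outcome on recruited participants, and for an analysis of those participants the concern applies.

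Second, the characteristics list may be illustrative. The article also uses the same abbreviation loosely elsewhere, the sentence on baseline comparison carries no list of its own, and a full covariate set is commonly left to the analysis plan. This stands in part. It rules out saying that a cognitive imbalance would go wholly unseen and unadjusted, since recorded dementia is a coarse marker and adjustment is provided for. It does not explain why the one variable on which selection acts goes unnamed where the list is spelled out.

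Third, the facilitator may exclude as readily as admit. This stands. A reader might infer that the step inflates, or dilutes, the intervention effect; neither direction follows from the text.

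Fourth, the outcomes most exposed are hard to repair. Interviews are analysed by content, and surveys are anonymous. This stands, and it limits adjustment to record-linked outcomes. Survey samples also differ by in-person versus postal invitation, which a cognitive score would not address.

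**Conclusion.** The point holds in limited form and is minor. The only named formal assessor of doubtful capacity exists in one arm, so recruited participants may differ by arm in borderline cognition. The stated baseline list would show this only through recorded dementia. The direction is unknown and the documents do not give the size. The range of 0.15 to 3.0 points, set against the planned 10, rests wholly on assumed shares and completion rates. Its lower end is negligible. The conclusion concerns record-linked outcomes in recruited participants, not the all-admissions audit. It assumes that control sites have no equivalent assessor, which the article implies but does not state.

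**What to change.** 1. Add the admission MOCA (or MMSE) score to the baseline comparison and to the adjustment covariates for record-linked participant outcomes: directive completion among the recruited 144 + 144, and concordance where linked. Under the article's selection rule a covariate stays only if associated with the outcome at the 10% level, so say whether the score is kept regardless.
2. Report by arm the numbers screened, in the 10–24 band, formally assessed, cleared and excluded. For the anonymous surveys, use these counts to qualify the comparison, since adjustment is not possible.
3. Do not plan a sensitivity analysis that drops facilitator-cleared participants from the intervention arm unless it is confirmed that control patients with doubtful capacity are not approached. If control invitations are ungated, that analysis would make the arms less alike.

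The cost is some wording, extraction of a score the article says is already taken, and a screening tally. No new patient procedure is needed. The downsides are the extraction work and incomplete scores at some sites.

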### Sample size calculation

Power calculations were conducted to determine the sample size required to detect a change of at least 10% in the primary outcome; that being the proportion of completed NSW ACDs. Change was defined as the difference between the proportion at baseline, assumed to be 5% and at follow-up. Setting alpha at 5%, power at 80% and assuming a non-response rate of 25%, a sample size of 288 is needed (144 in intervention sites and 144 in control sites). Given an average admittance rate of at least 10 per week per site and over a six-month period, there is almost complete surety that the study will not be under-powered.

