**Methods:**

The aim of this study is to investigate the effects of normalising ACP in acute and community settings with the use of specially trained normalisation agents. This is a quasi-experimental study, involving 16 sites (8 intervention and 8 control) in two health districts in Australia. A minimum of total 288 participants will be recruited (144 intervention, 144 control). We will train four registered nurses as normalisation agents in the intervention sites, who will promote and facilitate ACP discussions with adult patients with chronic conditions in hospital and community settings. An audit of the prevalence of ACP and Advanced Care Directives (ACDs) will be conducted before and after the 6-month intervention period at the 16 sites to assess the effects of the ACP service delivered by these agents. We will also collect interview and survey data from patients and families who participate, and healthcare professionals who are involved in this service to capture their experiences with ACP.

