**Fig. 1 Fig1:**
[figure not shown]
Research flow chart

ACP will be normalised into practice for 6 months by RN ACP facilitators (normalisation agents) in nominated wards/units in acute and community settings in two Local Health Districts (LHDs). Pre and post measures (the number of people who have ACDs in medical records, Resuscitation plan, any records or notes about ACP discussion and documentation, and the concordance between the expressed wishes and the care delivered) will be obtained for the two groups. Post qualitative data (textual data, individual/focus group interviews with patients, SDMs and staff participants) will be collected and inform the challenges, strategies and implications for future policy and practice.

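### The 288 is sized for one 5% v 15% comparison, while the text defines a change over time and both groups are measured twice; at the stated minimum with 25% non-response, no between-group contrast reaches 80% two-sided power

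*Protocol article*

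**What the plan says.** The Sample size calculation section of the protocol article aims to "detect a change of at least 10% in the primary outcome; that being the proportion of completed NSW ACDs". It continues: "Change was defined as the difference between the proportion at baseline, assumed to be 5% and at follow-up". The result is "Setting alpha at 5%, power at 80% and assuming a non-response rate of 25%, a sample size of 288 is needed", split as "144 in intervention sites and 144 in control sites". The section does not say whether the test is one- or two-sided, what the control sites are assumed to do, or whether 144 applies to each period. The Abstract repeats the figure as a floor: "A minimum of total 288 participants will be recruited (144 intervention, 144 control".

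The Design section says that pre and post measures "will be obtained for the two groups". The audit section under Data collection takes them from the records of everyone admitted in the two months before the intervention and in the six months of the intervention. Under Quantitative data analysis, "multi-level regression models with mixed effects will be built to estimate interventional effect"; no group-by-period term is named. The Discussion states that the study has good power for the primary outcome.

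**The concern.** A 5% to 15% calculation has two samples. Either they are baseline and follow-up, or they are intervention and control. The paragraph defines the first pair and allocates to the second. If the effect is a change and is judged against control sites, the estimate is a difference between two changes. It then carries the sampling error of four proportions, and a formula with two will overstate power.

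At stake is the one number given as sufficient for 80% power. The paragraph also sets no required size for the baseline audit, although any change-based contrast depends on it.

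**Working it through.** **Inputs from the Sample size calculation section.** Baseline 5%; change of 10, read as percentage points, so 15% at follow-up; alpha 5%; power 80%; non-response 25%; 144 per group; at least 10 admissions per week per site. There are eight sites per group (Table 2).

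**Assumptions not in the documents.** Control sites stay at 5%, patients are independent, there is no clustering, and power is by the normal approximation on the risk-difference scale.

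**1. Reproducing 288.** Unpooled two-proportion formula: n = (z_alpha + z_power)² × [0.05 × 0.95 + 0.15 × 0.85] / 0.10², with variance sum 0.0475 + 0.1275 = 0.175.
- One-sided: 108.2 per group; 108.2/0.75 = 144.3. This matches 144 with every stated input.
- Two-sided: 137.4 per group; 137.4/0.75 = 183.1. No match.
- Two-sided, pooled: 141 per group before non-response, which is near 144, but 188 per group (376 in total) after it. It comes close only if the stated 25% is left out.

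Each route to 144 is one comparison of two proportions.

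**2. Difference between the groups' changes, equal cells.** Variance = (3 × 0.0475 + 0.1275)/n = 0.27/n; power = Φ(0.10/SE − z_alpha).
- n = 108 per group per period (144 less 25%): SE = 0.050, z = 2.00, power 51.6% two-sided, 63.9% one-sided.
- n = 144: SE = 0.0433, z = 2.31, power 63.7% two-sided, 74.7% one-sided.

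For 80% power, n = (z_alpha + z_power)² × 0.27/0.01 = 211.9 per cell two-sided or 166.9 one-sided. The ratio to the single comparison is 0.27/0.175 = 1.54.

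**3. Same contrast, baseline from the full audit.** If the stated accrual also applies before the intervention, 10 × 8 sites × 8.67 weeks gives about 693 baseline records per group. Variance = 2 × 0.0475/693 + 0.175/n_post.
- n_post = 108: SE = 0.0419, power 66% two-sided, 77% one-sided.
- n_post = 144: SE = 0.0368, power 78% two-sided, 86% one-sided.

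**4. Follow-up comparison of groups only.** SE = √(0.175/n).
- n = 108: SE = 0.0403, z = 2.48, power about 70% two-sided, 80% one-sided.
- n = 144: SE = 0.0349, z = 2.87, power about 82% two-sided.

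**5. Expected audit size.** About 693 records before and 10 × 8 × 26 = 2,080 after, per group. Power for the contrast in step 2 is then above 99%, ignoring clustering.

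**The case against.** The strongest reply is that no section names a difference-in-changes test. The planned models force in an intervention effect with no stated period term, and a 144/144 split fits a follow-up comparison in which 5% is the usual-care rate. On that reading the formula is applied correctly and only the wording is poor. This stands in part: the contrast is ambiguous. But the definition of change then does not describe the planned test, and 80% still requires a one-sided test that the text does not declare.

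Second, the baseline will not be held to 108 or 144 records, because every admission over two months is audited. This stands. It lifts power at the minimum follow-up size to 66–78% two-sided, and to 86% one-sided if all 144 are evaluable.

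Third, the 25% allowance may not apply to the audit, since presence or absence of ACP is read from records before consent is sought. That is fair, and with 144 evaluable a follow-up comparison has about 82% two-sided. The paragraph nonetheless states that 288 includes the allowance.

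Fourth, pairing the same patients across periods would change the figures: at 108–144 per group, two-sided power would run from about 53% to 98% depending on discordance. The plan describes audits of admissions in two separate windows and no paired analysis.

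A reader might infer that the study's power is simply 52–64%, or that it is underpowered. The documents support neither. The first needs a test they do not name and a baseline far smaller than the one they plan; the second ignores an expected accrual well above 288. Splitting 144 over both periods gives still lower figures (29–37% two-sided at 54–72 per cell), but nothing says the sample is split.

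**Conclusion.** The mismatch is real. The paragraph defines a change from baseline, allots its two samples to intervention and control sites, and carries no variance for the baselines or for the control group's change.

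The shortfall depends on the intended contrast. With the stated non-response, so 108 evaluable per group at follow-up, two-sided power is 52% for the difference in changes with an equal-sized baseline, 66% with the full audit baseline, and about 70% for follow-up alone. Only the last reaches 80%, and only one-sided. These figures rest on independent patients and controls steady at 5%. Clustering across the 16 sites is not included and would generally lower them.

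The fault lies in the stated minimum and its justification. At the stated accrual, and leaving clustering aside, the number of records is ample.

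**What to change.** In the Sample size calculation section, name the powered contrast, its sidedness and the assumed change in the control sites. Recalculate for that contrast and give the required audited records per group separately for the two-month pre window and the six-month post window. For the difference in changes with equal cells, that is about 212 evaluable records per cell two-sided or 167 one-sided, before any allowance for clustering.

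Restate or withdraw the 80% claim attached to 288, and amend the matching minimum in the Abstract. The Discussion's statement about power should rest on the expected audit size instead of 288.

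The cost is one recalculated paragraph and two consistent edits. No additional patients, staff or procedures are needed.

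### The 288 does not follow from the stated inputs under a two-sided test: that needs about 368–376, and 108 evaluable per group gives about 69% power, not 80%

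*Protocol article*

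**What the plan says.** Under Sample size calculation, the target is to "detect a change of at least 10% in the primary outcome; that being the proportion of completed NSW ACDs". The baseline is fixed in the next sentence: "Change was defined as the difference between the proportion at baseline, assumed to be 5% and at follow-up". Then: "Setting alpha at 5%, power at 80% and assuming a non-response rate of 25%, a sample size of 288 is needed", allocated as "144 in intervention sites and 144 in control sites". No formula is given, and nothing says whether the test is one- or two-sided. The Abstract treats the figure as a floor: "A minimum of total 288 participants will be recruited (144 intervention, 144 control"). The sample size section goes on to use the expected admission rate to say that under-powering is all but ruled out, and the Discussion repeats that power for the primary outcome is good.

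Under Quantitative data analysis, the significance level is given without sidedness: "All tests of significance will be set at 5" per cent. For unadjusted group comparisons, Fisher's "Exact test will be used for categorical outcomes". For the intervention effect itself, "multi-level regression models with mixed effects will be built to estimate interventional effect", with logistic regression for binary outcomes.

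**The concern.** Every input to the calculation is printed except the sidedness, so the result can be checked. With the usual two-sided reading the answer is well above 288. No one-sided test is mentioned anywhere, and the tests and models named in the analysis section are normally reported two-sided.

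At stake is the power claimed for the primary outcome. If the recruited minimum is reached and the assumed loss occurs, the chance of missing a true rise from 5% to 15% is about 31%, not the stated 20%, before clustering by site is considered. A null result would then be read as coming from a study with more power than it had.

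**Working it through.** **Inputs (all from Sample size calculation):** p1 = 0.05; p2 = 0.15 (5% plus 10 points); alpha = 0.05; power = 0.80 (z = 0.8416); non-response 25%; 144 per group. I take the comparison as two independent groups at follow-up, with control sites staying at 5%.

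Variance terms: p1(1−p1) + p2(1−p2) = 0.0475 + 0.1275 = 0.175. Mean proportion 0.10, so 2 × 0.10 × 0.90 = 0.18.

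**1. Reproducing the published figure.**
- One-sided, unpooled: n = (1.6449 + 0.8416)² × 0.175 / 0.10² = 108.2. Divided by 0.75: 144.3 per group, 288.5 in total. This is the printed number to within rounding. (Rounding 108.2 up to 109 first gives 146; the pooled formula gives 111, then 148; arcsine gives 105, then 140.)
- Two-sided with the inflation left out: 138 (unpooled) to 141 (pooled) per group, 276–282 in total. This is also close to 288.

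**2. Two-sided with all stated inputs.**
- Unpooled: n = (1.960 + 0.8416)² × 0.175 / 0.01 = 137.4, so 138. Then 138/0.75 = 184 per group, **368** in total.
- Pooled: n = [1.960 × √0.18 + 0.8416 × √0.175]² / 0.01 = (0.8315 + 0.3521)² / 0.01 = 140.1, so 141. Then 141/0.75 = 188 per group, **376** in total.
- Variants: arcsine 133, then 178 (356 in total); continuity-corrected 160, then 214 (428 in total); inflating the pooled 141 by × 1.25 gives 177 (354 in total).

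None of these is near 288. Against 376 the shortfall is 88/376 = 23%; against 368 it is 80/368 = 22%.

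**3. Power at the published size.** Evaluable after 25% loss: 144 × 0.75 = 108 per group. Pooled normal approximation: power = Φ[(0.10 × √n − z × √0.18) / √0.175].
- n = 108, two-sided: (1.0392 − 0.8315)/0.4183 = 0.496, so **69.0%**. Unpooled gives 70.0%; exact enumeration of the uncorrected chi-square test gives 71.9%.
- n = 108, one-sided: 79.3% (79.9% unpooled).
- n = 144, two-sided: (1.2000 − 0.8315)/0.4183 = 0.881, so **81.1%**.

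**4. Side note on Fisher's exact test.** Summing binomial probabilities over all tables with two-sided p ≤ 0.05 gives 63.0% at 108 per group and 77.6% at 144. These figures concern the unadjusted comparison only.

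Nothing above allows for clustering across the 16 sites. The article gives no intracluster correlation, so I have not put a figure on it. A positive correlation would lower all these powers.

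**The case against.** Five points can be made for the plan.

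*The number is only a minimum.* At 10 admissions per week per site, 26 weeks and 8 sites give about 10 × 26 × 8 = 2,080 admissions per group before eligibility and consent. The achieved sample may well be larger. That is true, but a minimum is a number at which the study may stop, so it should deliver the power claimed for it. Plentiful admissions do not repair the derivation.

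*The 25% loss may not touch the primary outcome.* The audit section checks all admitted patients' records for presence or absence of advance care planning before consent is sought; consent concerns the content. If the primary outcome comes from that first step, no one is lost to non-response and 144 per group gives about 81%. This stands, and it makes the 69% conditional. The 25% is nevertheless the article's own input.

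*The article speaks of a change from baseline, so a paired calculation might apply.* A two-sided McNemar calculation with an assumed 2% changing in the reverse direction does give 107.5/0.75 = 143.3. But no discordance rate is stated, and the audit covers patients admitted in two separate periods, so pairing is not described. This does not rescue the figure.

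*A reader might infer that a one-sided test must have been used.* The documents do not show that. Omitting the inflation from a two-sided calculation is an equally plausible origin.

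*A reader might also infer that the primary analysis has only 63% power because Fisher's exact test is planned.* The documents do not support that either: Fisher's test is listed for unadjusted comparisons, while a mixed-effects model estimates the intervention effect.

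**Conclusion.** The point holds as an error in the stated sample size and power. With all the printed inputs and a two-sided 5% test, 368–376 participants are needed, against 288. The published figure is explained either by an undeclared one-sided test or by a missing non-response inflation. In the first case the size does not match a conventional two-sided analysis; in the second the claimed allowance for non-response was not made. Either way the paragraph needs correcting.

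Two-sided power is about 69% at 108 evaluable per group and about 81% if all 144 are analysed. This rests on two independent groups, 5% against 15%, the article's own 25% loss for the lower figure, and no clustering. It does not establish that the trial will in fact run at 69%: that depends on how many are enrolled or audited, and on whether non-response affects the primary outcome at all.

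**What to change.** State in the sample size section that the test is two-sided at 5%, name the formula, and then take one of two routes:

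1. If the 25% non-response applies to the primary outcome, restate power as about 69% at 108 evaluable per group, before the design effect.
2. If the primary outcome is read from the record audit that precedes consent, say so, remove the 25% term, and restate power on the number audited (about 81% at 144 per group, before the design effect).

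Amend the assurance about under-powering at the end of the sample size section, and the matching claim in the Discussion, so that they agree with the restated figure.

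The cost is one paragraph of wording and, under the first route, a less favourable stated power. Correcting the statement needs no extra recruitment. Keeping both 80% power and the 25% allowance would be a separate choice, and would raise the minimum to about 368–376 before clustering.
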